## Methods

This section is presented according to the SPIRIT 2013 statement in defining standard protocol items for clinical trials [40]. The completed CONSORT EHEALTH checklist [16] is found in Multimedia Appendix 1.

### Study Design and Settings

The study design is a two-group parallel multicenter RCT testing the effect of an experimental group that is receiving access to a 4-week Web-based tailored nursing intervention (TAVIE en m@rche) and a brief “booster” at 8 weeks, compared with a control group that is receiving access to hyperlinks of publicly available websites on increased steps per day. Study settings are at four major teaching hospital centers in Montreal, Canada.

### Eligibility Criteria

Patients are eligible if they are home the third week after an ACS-related hospitalization, have no serious medical condition that would impede adhering to moderate intensity physical activity, report access in any location to a computer with a USB port that is connected to the Internet, and report the ability to read and speak French. Patients are ineligible if they self-report sufficient physical activity during 6 months prior to the hospitalization where they are recruited (ie, performed at least 150 minutes [30 minutes 5 days a week] of moderate intensity physical activity per week or at least 75 minutes [25 minutes 3 days per week] of vigorous intensity physical activity per week), have documented New York Heart Association Class III-IV heart failure, or reported planned involvement in intensive regular clinical follow-up (eg, an outpatient heart failure clinic) during TAVIE en m@rche. One hospital center asked that those who are eligible for participation in their onsite secondary prevention program (ie, new diagnosis of ACS and age <75 years) be ineligible for study participation to avoid delivery of parallel secondary prevention interventions at that center.

### Interventions

Both groups receive usual care from hospital entry to return home. At all four recruitment centers, from hospital entry to hospital discharge, usual care consists of brief counseling by hospital staff on discharge issues such as new medications and their side effects and on health behavior changes such as progressively increasing physical activity at home. Printed materials are provided as teaching aids to complement the brief counseling. As well, patients receive referrals to onsite or community-based secondary prevention programs.

After hospitalization, all centers offer secondary prevention programs, but at varying doses. All offer an educational group program on the topic of cardiac risk factors and health behaviors aimed at reducing these risk factors, but the number of sessions varies between one and eight across the four centers. Also, three of the four centers offer onsite supervised exercise programs, but the number of sessions vary between one to three times per week. Two of the programs are 12 weeks in duration, and the other lasts 1 year.

#### Control Group

The control group receives a list of four hyperlinks on a unique webpage of available online information that is Canadian, French, and that included information on walking. Three major Canadian nonprofit or public organizations are included: Montreal Heart Institute, Heart and Stroke Foundation, and Canadian Society for Exercise Physiology. In addition, because key recommendations on walking post‒ACS-related hospitalization were derived from a patient education booklet published by the Montreal Heart Institute that is available online, the walking program in this booklet is also included in the list of hyperlinks. All websites provide information in text format without the use of videos.

#### Experimental Group

The experimental group receives access to TAVIE en m@rche. The central feature of TAVIE en m@rche is the prerecorded videos of a nurse (see Multimedia Appendix 2) who presents the fully automated tailored intervention content delivered according to patients’ baseline assessments of autonomous motivation, perceived competence, and walking behavior. Other modes of delivery include online text that appears beside the videos to allow simultaneous reading of the video’s content, and downloadable PDF files referred to by the nurse. Access to TAVIE en m@rche starts at randomization between the fourth and fifth week after hospitalization, which depends on when the baseline online assessment is submitted. The suggested completion time of the intervention is 4 weeks but access to the intervention ends at 11 weeks postrandomization. An additional brief “booster” is added at 8 weeks postrandomization. We estimate about 60-75 minutes is sufficient to complete the intervention. TAVIE en m@rche consists of 73 videos, each lasting on average nearly 1 minute with most (n=68) lasting less than 2 minutes. The TAVIE platform has simple webpage layouts and is easy to navigate [41].

The intervention goal is to encourage a progressive increase in walking behavior, up to the recommended 150 minutes per week at moderate intensity, which is determined by an adapted version of the Borg Rating of Perceived Exertion [42]. This walking level is recommended to all patients at discharge for an ACS-related hospitalization by their treating physician unless a contraindication is present such as comorbid physical condition or an environmental constraint. Such patients are ineligible for study participation.

The intervention is based on a theoretical framework that integrates SBNC with SDT. SBNC focuses on nursing values such as fostering a collaborative partnership with the person, supporting the person’s self-determination in their decisions and actions, and working with the person’s strengths in the aim of achieving health and healing. The SDT on human motivation specifies theoretical constructs for physical activity to be targeted by the intervention strategies and to drive the tailoring process. The intervention strategies are specifically targeted toward increasing self-reported perceived autonomy support, autonomous motivation, and/or confidence (combined perceived competence and barrier self-efficacy).

The appeal of using videos as the main mode of delivery, rather than text-only format, is the greater ability to convey the strengths-based nursing way of being that is manifested in part by nonverbal behaviors such as tone of voice (eg, energetic vs neutral) and body language (eg, smiling vs a sincere nonjudgmental expression), and by verbal behaviors (ie, the nurse’s script). This script, consistent with both SBNC and SDT, drawn from our past literature review [43], followed five global strategies: being collaborative, being strengths-focused, providing choice, offering rationale, and expressing empathy. These global strategies can be thought of as the fabric in which the entire intervention content is interwoven. As such, we expect that the use of videos instead of text-only format will be more interesting and motivating to participants because the SBNC way of being will be better conveyed.

The intervention consists of four specific strategies targeting increasing perceived autonomy support, autonomous motivation, and/or confidence aimed at increasing walking behavior: Strategy (1) Providing information and feedback to build motivation and confidence; Strategy (2) Exploring reasons to build motivation; Strategy (3) Exploring personal strengths to build confidence; and Strategy (4) Developing an action plan to build and consolidate motivation and confidence. These strategies are operationalized by 19 behavior change techniques. The terminologies of those 19 techniques were made consistent with those of the CALO-RE taxonomy [44] (Table 1). These behavior change techniques were drawn from three main literary sources: (1) SDT-based physical activity face-to-face or Web-based interventions and Motivational Interviewing due to its consistency with SDT [45], (2) facilitators of physical activity such as improved cardiac health and quality of life, and barriers of physical activity such as lack of time and the presence of fatigue and depressive symptoms found in cardiac patients, and (3) two patient education booklets on the secondary prevention of ACS [42,46]. The content validity of comparing intervention strategies (global and specific) with the theoretical background was done by the Université de Montréal scientific PhD jury of the first author. One cardiac nurse reviewed the operationalization of the entire intervention, and two clinical kinesiologists in secondary prevention reviewed the operationalized information on walking.

**Table 1 table1:** Specific strategies, intermediate intervention goals, behavior change techniques, and targeted SDT variables.

Specific strategy	Intermediate intervention goal	Behavior change technique	Targeted SDT variable^a^
1. Providing information and feedback on walking behavior	To help patients build or consolidate motivation and confidence to increase walking behavior or maintain sufficient walking behavior	1.1 Provide information on consequences of behavior in general by providing information on potential advantages of physical activity through walking	Perceived autonomy support from the intervention Autonomous motivation
		1.2 Provide instruction on how to perform the behavior of attaining the recommended minutes per week of physical activity through walking	Perceived autonomy support from the intervention Confidence
		1.3 Provide feedback on performance tailored to minutes per week of walking in the past 7 days	Perceived autonomy support from the intervention Confidence
2. Exploring reasons to increase walking behavior	To help patients build motivation to increase walking behavior	2.1 Motivational interviewing, asking evocative questions to explore advantages of increasing walking behavior, and to explore goals and values^c^	Perceived autonomy support from the intervention Autonomous motivation
		2.2 Motivational interviewing, sharing a list of potential reasons to increase walking behavior^c^	Perceived autonomy support from the intervention Autonomous motivation
3. Exploring strengths	To help patients build confidence to increase walking behavior	3.1 Motivational interviewing, asking evocative questions to explore strengths^c^	Perceived autonomy support from the intervention Confidence
		3.2 Motivational interviewing, sharing a list of potential strengths^c^	Perceived autonomy support from the intervention Confidence
4. Developing an action plan	To help patients consolidate their motivation and confidence to increase walking behavior or maintain sufficient walking behavior	4.1 Provide instruction on how to perform the behavior of perceived exercise exertion assessment and planning walking in four steps	Perceived autonomy support from the intervention Confidence
		4.2 Teach to use prompts/cues using flash card of perceived exertion and the four steps	Perceived autonomy support from the intervention Confidence
		4.3 Goal setting using SMART goals	Perceived autonomy support from the intervention Confidence
		4.4 Provide information on consequences of behavior in general by providing information on potential advantages of walking, and how to make walking enjoyable	Perceived autonomy support from the intervention Autonomous motivation
		4.5 Teach to use prompts/cues using flash card of SMART goals and reasons for walking	Perceived autonomy support from the intervention Autonomous motivation Confidence
		4.6 Prompt self-monitoring of behavior of SMART goals	Perceived autonomy support from the intervention Autonomous motivation^b^ Confidence
		4.7 Provide information on where and when, and instruction on how to perform the behavior using practical tips to increase walking behavior or to maintain sufficient walking behavior	Perceived autonomy support from the intervention Confidence
		4.8 Prompt review of the identification of behavioral goals (SMART goals, and reasons for walking)	Perceived autonomy support from the intervention Autonomous motivation Confidence
		4.9 Barrier identification/problem solving	Perceived autonomy support from the intervention Autonomous motivation^b^ Confidence
		4.10 Plan social support to elicit support from significant others in the attainment of increasing walking behavior or maintaining sufficient walking behavior	Perceived autonomy support from the intervention Perceived autonomy support from a significant other
		4.11 Provide an example of action planning	Perceived autonomy support from the intervention Autonomous motivation^b^ Confidence
		4.12 Provide feedback on performance (action plan and walking behavior)	Perceived autonomy support from the intervention Confidence

^a^Perceived autonomy support from the intervention is targeted throughout because the global strategies (Being Collaborative, Being Strengths-Focused, Providing Choices, Offering Rationale, and Expressing Empathy), which are consistent with both SBNC and SDT, are integrated within each specific strategy.

^b^Autonomous motivation targeted 4.6 in the enjoyment in monitoring the accomplishments of a SMART goal; 4.9 in two barriers: (1) not having enough time to walk, and (2) having no reason to walk; and 4.11 in the example of reasons for increasing walking behavior within an action plan.

^c^Motivational Interviewing is reported here as behavior change techniques consistent with the CALO-RE taxonomy and is limited to open-ended questions consistent with Motivational Interviewing, without the back-and-forth aspect of face-to-face counseling found in an interview.

The strategies are conveyed through a set of videos that build toward participants’ commitment to developing their own action plan. The order of the strategies is determined by the primary static tailoring method that is driven by participants’ baseline self-reported autonomous motivation (low vs high), confidence (low vs high), and walking behavior, which resulted in four tailored profiles: A, B, C, and D (Figure 1). Profiles A, B, and C are assigned from scores that are below the recommended 150 minutes per week of walking. Profile A receives Strategies 1 (information), 2 (reasons), 3 (strengths), and 4 (action plan) because this profile is low in motivation and confidence. Profile B receives Strategies 1 (information), 2 (reasons), and 4 (action plan) because this profile is low in motivation. Profile C receives Strategies 1 (information), 3 (strengths), and 4 (action plan) because this profile is low in confidence. Profile D receives Strategies 1 (information), and 4 (action plan) because this profile is high in motivation and confidence. In addition, participants who attained the recommended minutes per week of walking between hospital discharge and baseline receive Profile D.

Secondary methods are the use of tailored messages based on “yes” versus “no” responses to questions after intervention login on identifying symptoms of exercise intolerance in the past 7 days (Introduction). Participants who respond “yes” to having identified symptoms of exercise intolerance are provided an onscreen video message asking them to not initiate the intervention, to consult a free 24-hour province-wide phone service for general health problems if the symptoms are nonurgent, or to call 9-1-1 or go to the emergency department if the symptoms are urgent, and then to log out of the intervention. Two weeks later, participants are asked to log in to the intervention, and only if no symptoms of exercise intolerance are identified by the participant, they are invited to continue the intervention. Static tailored messages on walking behavior (ie, feedback on performance) are also provided to participants in all four profiles (Strategy 1 information) based on their responses of walking behavior assessed only at baseline. Other tailored messages based on “yes” versus “no” responses to questions after intervention login pertain to the identification of personal reasons for walking (Strategy 2 reasons), personal strengths (Strategy 3 strengths), personal goals that are SMART (Specific, Measurable, Attainable, Realistic, and within a Timeframe) (Strategy 4 action plan), social support, and solutions to barriers (Strategy 4 action plan).

**Figure 1 figure1:**
[figure not shown]
Schema of the intervention’s general and per profile introductions, and the four specific intervention strategies.

### Timeline and Procedures

The study duration is 16-17 weeks, from hospitalization (-T2) to the last assessment at 12 weeks postrandomization (T3). We estimate that 4 hours in the experimental group and 2.5 hours in the control group are needed to participate in the study, which includes time spent in either experimental or control interventions, and the completion of the questionnaires (Table 2).

**Table 2 table2:** Schedule of enrollment, interventions, and assessments.

				Minutes per patient	Recruitment	Baseline	Randomization	Interventions	Follow-up 5 wks	Follow-up 12 wks
Activity			Items		-T2	-T1	T0	T1	T2	T3
**Eligibility screening**										
	Patient lists			N/A	x					
	Inclusion/exclusion interview			~10	x					
	Screening log			N/A	x					
Consent and signing				~30	x					
Instruction to wear accelerometer and complete questionnaires				~10		x				
Randomization and allocation to group				~1			x			
Access to experimental or control group interventions				~60-75				x		
Documentation				N/A	x	x	x	x	x	x
**Assessments in-hospital**										
	Sociodemographic data and depression questionnaire		19	~15	x					
	Give and explain accelerometer wear			~10	x					
	Clinical data (eg, history, tests, events, and cardiac risk factors)			N/A	x					
**Assessments at home**										
	Intervention adherence			N/A				x		
	Primary outcome (X) steps/day			N/A		X			x	X
	**Questionnaires**			~30-45						
		Self-reported physical activity and location of accelerometer wear	7			x			x	x
		Perceived autonomy support of significant other	6						x	
		Perceived autonomy support of websites	6						x	
		Autonomous and controlled motivations	12			x			x	
		Perceived competence	4			x			x	
		Barrier self-efficacy	8			x			x	
		Quality of life	27			x				x
		Smoking status	1			x				x
		Medication adherence	4			x				x
		Secondary prevention program enrollment	2							x
		Angina frequency	2			x				x
		Fatigue	7			x				
	**Clinical data**									
		Emergency visits and hospitalizations		N/A						x

Recruitment (-T2) takes place in-hospital. Potential participants are identified through patient lists during hospitalization, and we then proceed with preliminary eligibility screening using patients’ medical charts (Figure 2). Eligibility screening, rather than being based on a 24-hour and 7-day a week schedule, is based on the recruiters’ irregular schedules, which vary depending on their availability to present at one of the four sites or on other constraints such as work (academic or other) unrelated to recruiting. When potential participants are approached in hospital, eligibility is confirmed (ie, inclusion/exclusion based on in-person interview), and the study protocol is explained. After signed consent is obtained, self-administered paper questionnaires on sociodemographic data and depressive symptoms are completed. Participants are then given an accelerometer and an open prepaid envelope to use when sending it back to the researcher at the end of the study. After hospital discharge, clinical data are collected from the medical chart.

Baseline (-T1) is at the beginning of the third week posthospital discharge. In conjunction with an email, participants are contacted by phone to confirm their willingness to participate. This email includes a hyperlink to download and install the software into the participants’ computers, allowing the accelerometer data to be synced to the company’s server. Thereafter, the data can then be downloaded into the researcher’s computer. During the same phone call, participants are instructed to wear the accelerometer daily for 7 days from awakening to bedtime. After 7 days of accelerometer wear, a second email is sent that includes a hyperlink to access the first online questionnaire. Although we expect most participants to complete the baseline accelerometer wear followed by the online questionnaire within 1 week, a maximum window of 2 weeks is allowed to complete baseline assessments.

Randomization (T0) and allocation to the experimental or control groups occur upon submission of the baseline questionnaire at the fourth or fifth week posthospital discharge, allowing participants the window of 2 weeks to complete baseline assessments. Each participant receives, by automated email from the TAVIE platform, access to either TAVIE en m@rche or the control group involving publicly available websites.

Interventions (T1) start immediately after allocation to the experimental or control groups. Follow-ups at 5 weeks (T2) and 12 weeks (T3) postrandomization are planned. At both follow-ups, participants in both groups (experimental and control) are sent an email with instructions to wear the accelerometer for 7 days. If participants accept, a brief text message is sent to remind them to read the email. After 7 days of accelerometer wear, a second email is sent to complete the online questionnaires. In addition, at the end of data collection, participants are instructed to return the accelerometer by mail via the prepaid envelope provided. During participation, the first author is available by phone and email to resolve technical difficulties in accessing the intervention or questionnaires.

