### Study Aim and Hypotheses

The aim of this RCT is to evaluate in insufficiently active ACS patients, the effect of a fully automated, Web-based tailored nursing intervention (TAVIE en m@rche) on increased steps per day. Our primary hypothesis is that ACS patients in the experimental group receiving TAVIE en m@rche compared with the control group receiving hyperlinks to publicly available websites will demonstrate a greater increase in change in steps per day between randomization and 12 weeks (H1). Secondary hypotheses are a greater increase in change in steps per day between randomization and 5 weeks (H2), and in energy expenditure for walking and moderate to vigorous physical activity between randomization and 5 weeks, and randomization and 12 weeks (H3 to H6).

We are interested in assessing if the change in SDT variables immediately postintervention at 5 weeks will explain the hypothesized increase in steps per day at 12 weeks. Therefore, we will explore the mediating role of the SDT constructs (perceived autonomy support, controlled and autonomous motivations, perceived competence) and barrier self-efficacy on the effect of TAVIE en m@rche on increased steps per day at 12 weeks (H7 to H11 respectively).

We will also explore the effect of TAVIE en m@rche at 12 weeks on improved quality of life (global, emotional, physical, and social), smoking, medication adherence, secondary prevention program attendance, emergency visits, and hospitalizations (H12 to H20). The potential moderating role of sex on the effect of TAVIE en m@rche on steps per day at 12 weeks will also be explored (H21). Finally, we expect no adverse effect, which is represented by an equal level of angina symptom frequency at 12 weeks in both groups (H22).

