#### Outcomes of Theoretical Variables

Two outcomes assessed only at 5 weeks for Perceived autonomy support (PAS) were drawn from a French version of the Important Other Climate Questionnaire: (1) from a significant other (PAS-SO) and (2) from the intervention (PAS-WEB). These measures assess autonomy support felt from a significant other (PAS-SO) and from either research website visited (PAS-WEB). The two scores are the mean of responses of 6 items for each PAS (significant other [SO] vs intervention [WEB]) rated between “not at all true” (1) and “very true” (7). Higher scores represent greater levels of PAS. Reported Cronbach alphas across three assessments were between .86 and .89 [54].

Self-determined motivation is assessed at baseline and 5 weeks by the French version of the Treatment Self-Regulation Questionnaire. This measure assesses reasons to attain the recommendation of walking 150 minutes per week. We retained the 12 items that assess controlled motivation (6 items) and autonomous motivation (6 items). The two scores are the mean of responses of 6 items for each motivation (controlled vs autonomous) rated between “not at all true” (1) and “very true” (7). Higher scores represent greater levels of controlled and autonomous motivation. Reported Cronbach alphas across four populations were between .73 and .91 for controlled motivation, and between .85 and .93 for autonomous motivation [55].

Perceived competence is assessed at baseline and 5 weeks by the French version Perceived Competence Scale [53]. This measure assesses confidence to attain the recommendation of walking 150 minutes per week. The score is the mean of responses of 4 items rated between “not true at all” (1) and “very true” (7). Higher scores represent greater levels of perceived competence. Reported Cronbach alphas across two assessments were .93 and .96 [54].

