Barrier self-efficacy is assessed at baseline and 5 weeks by the French version Barrier Self-Efficacy Scale for cardiac patients [35]. This measure assesses confidence to walk for the recommended 150 minutes per week even if one or more of eight barriers listed are experienced. We retained 8 of the 9 items. The item removed referred to the barrier of experiencing angina or chest pain. Instead of overcoming this barrier, we expect that participants treat the pain and consult a health care professional if the pain is not relieved instead of continuing to increase their walking behavior. The score is the mean of responses of 8 items rated between “(0%) not at all confident” and “(100%) very confident.” Higher scores represent greater levels of barrier self-efficacy. A reported Cronbach alpha was .86 in the original 9-item scale [35].

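### The 5-week mediators are measured after part of the walking change they are meant to explain, and the stated mediation analysis makes no use of the 5-week step count

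*Protocol article*

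**What the plan says.** The hypotheses section (Study Aim and Hypotheses) sets the purpose: "we will explore the mediating role of the SDT constructs" and barrier self-efficacy, to see whether the "change in SDT variables immediately postintervention at 5 weeks will explain the hypothesized increase in steps per day at 12 weeks". These are H7 to H11. The same section also predicts, as H2, a greater step gain by 5 weeks.

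Timeline and Procedures fixes the calendar: "Follow-ups at 5 weeks (T2) and 12 weeks (T3) postrandomization are planned". Access to the intervention starts straight after allocation. At both follow-ups the accelerometer week comes first: "After 7 days of accelerometer wear, a second email is sent to complete the online questionnaires".

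Outcomes of Theoretical Variables and Table 2 give one post-randomization measurement of each mediator: "Perceived competence is assessed at baseline and 5 weeks by the French version Perceived Competence Scale" and "Barrier self-efficacy is assessed at baseline and 5 weeks by the French version Barrier Self-Efficacy Scale for cardiac patients". Motivation follows the same two times. Perceived autonomy support is measured at 5 weeks only. The competence items concern walking itself: "This measure assesses confidence to attain the recommendation of walking 150 minutes per week". The self-efficacy and motivation items refer to the same walking target.

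The primary outcome is change in steps from randomization to 12 weeks, so it contains the change in weeks 0 to 5. Statistical Methods describes the mediation analysis as a series of one-way analyses of variance with Bonferroni adjustment and mentions no role for 5-week steps. The Conclusion lists as a strength that the constructs may account for the effect on the primary outcome.

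**The concern.** A mediation reading needs the mediator to move before the behaviour it explains. Here the outcome window opens at randomization, the intervention starts at once, and H2 expects more walking by week 5. The mediators are recorded only after that walking has been counted. A participant who already walks more has good reason to report more confidence in reaching 150 minutes a week. Because walking at week 5 and week 12 will be correlated within a person, such a score would predict 12-week steps even if it had no effect on them.

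The 5-week step count, which could separate the two explanations, is collected but has no stated place in the mediation analysis. At stake is the interpretation of H7 to H11, which the article presents as a strength of the trial. The test of H1 is not at stake.

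**Working it through.** **Inputs from the protocol.** Difference 1500 steps/day, SD 2824, two-sided 5%, 80% power, 23% attrition, 57 completers per group (Sample Size Calculation).

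**The plan's own figure.** n per group = 2 × (1.96 + 0.842)² × (2824/1500)² = 2 × 7.85 × 3.544 ≈ 55.6, so 56; the t-test version gives 56.6, so 57. Then 57/0.77 = 74.03, about 74 per group and 148 in total. This reproduces and supplies N = 114 completers. The protocol gives no figure for mediation.

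**Assumptions, not in the documents.**
- c: within-arm correlation of step change to week 5 with the 5-week mediator, caused entirely by walking; 0.2 to 0.4.
- r: within-arm correlation of step change to week 5 with step change to week 12; 0.5 to 0.7.
- f: share of the 1500-step effect present at week 5; 0 to 1.
- The mediator has no effect on steps.
- The mediator-to-steps path is tested given group, the usual form.

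**Path from mediator to 12-week steps, given group.** The within-arm correlation is c × r. Rejection rate ≈ Φ(arctanh(cr) × √110 − 1.96).
- r = 0.5, c = 0.2: arctanh(0.10) × 10.49 = 1.05; Φ(−0.91) = 18%.
- r = 0.7, c = 0.4: arctanh(0.28) × 10.49 = 3.02; Φ(1.06) = 86%.

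Simulation of 3000 trials per cell, in each case for c = 0.2, 0.3, 0.4:

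| r | path falsely significant | with 5-week step change in the model |
|---|---|---|
| 0.5 | 18%, 35%, 56% | about 5% |
| 0.7 | 32%, 62%, 85% | about 5% |

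f does not enter this formula. Simulated rates are essentially the same when none of the effect is present at week 5.

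**Both paths together.** A mediation result also needs an effect of group on the mediator. With f = 1 the induced shift is c × 1500/2824 = 0.53c SD, with standard error √(2/57) = 0.187.
- r = 0.7, c = 0.4: 0.212/0.187 = 1.13; Φ(1.13 − 1.96) = 20%; 20% × 86% ≈ 17% (simulated about 16%).
- r = 0.5, c = 0.2: 0.106/0.187 = 0.57; Φ(0.57 − 1.96) = 8%; 8% × 18% ≈ 1.5% (simulated about 2%).

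For c = 0.2, 0.3, 0.4 the simulated joint rates are about 2%, 5%, 12% at r = 0.5 and about 3%, 7%, 16% at r = 0.7.

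If the intervention also raises the mediator directly by an assumed 0.4 SD, the joint rates at r = 0.7 are about 26%, 51% and 77%. For c = 0.4: (0.212 + 0.4)/0.187 = 3.27; Φ(1.31) = 90%; 90% × 86% ≈ 77%.

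**Size of the false indirect effect.** Product of paths = (c × f × 1500/2824) × (c × r × 2824) = c² × r × f × 1500. With c = 0.4, r = 0.7, f = 1: 0.16 × 0.7 × 1500 = 168 steps/day (11%). With a stronger c of 0.5: 0.25 × 0.7 × 1500 = 262 (17%). With f = 0 it is zero. Adding step change to week 5 brings it to about zero throughout.

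**Bonferroni.** With an assumed divisor of five (alpha 0.01), c = 0.3 gives a falsely significant mediator path in about 36% (r = 0.7) and 15% (r = 0.5). Both paths at r = 0.7, f = 1 and no direct shift: about 0.3%, 1.2% and 5% for c = 0.2, 0.3, 0.4.

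**The case against.** The order for H7 to H11 is formally correct: mediators at 5 weeks, outcome at 12. That stands, so it would be wrong to say that the mediators come after the outcome. The weakness is the missing control for earlier walking.

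A reader might infer that most of the walking change is over by week 5. The documents do not say so. The goal is a gradual increase, access lasts to week 11, a booster comes at week 8, and 12 weeks was chosen to test persistence. Only part of the change can be claimed. The share affects the size of a false indirect effect and the joint rate, but not the mediator-to-steps path.

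A reader might also take the 18% to 86% as the rate of false mediation findings. It is the rate for one path. The joint rate is far lower unless the intervention also moves the mediator directly, and Bonferroni lowers it further.

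Nor do the documents show that a causal claim would be made. H7 to H11 are exploratory, and the Conclusion says only that the constructs may explain the effect.

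Autonomy support asks about choice, rationale and empathy from a website or another person. Walking more is not an obvious cause of higher scores there.

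Finally, the covariates of an exploratory model are often left to the analysis plan. But this article itself fixes the measurement order, the mediator time point, the outcome window and the model family, and the point concerns those.

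**Conclusion.** The concern holds in limited form. The 5-week mediators follow the 5-week step count and part of the change they are meant to explain, and the stated analysis cannot tell confidence or motivation that produces walking from confidence or motivation produced by it. Misreading is possible, not certain. It is most plausible for perceived competence, barrier self-efficacy and motivation.

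If the mediator has no effect on steps, the false-positive rate is about 18% to 86% for the mediator-to-steps path. It is about 2% to 16% for both paths jointly when the full effect is present by week 5. It reaches about 77% at the upper end if the intervention also shifts the mediator by 0.4 SD. All these figures rest on assumed correlations that the documents do not give. The primary analysis and sample size are untouched.

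**What to change.** For H7 to H11, add a model of 12-week steps on group and the 5-week mediator, given baseline and 5-week steps. Report it beside the model without 5-week steps, and describe the latter as an association only. The added model asks whether the mediators predict later walking beyond what had been achieved by week 5.

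The cost is one covariate from data already collected and a sentence or two of text. The downside should be stated with the result: the adjusted model removes mediation already complete by week 5, so it is conservative if motivation rises early, drives walking early and the gain persists. That is why both models are needed.

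Leave the questionnaire timing alone. Moving the items ahead of the wear week mid-trial would break comparability with baseline, which also has wear first, and with participants already past T2. It would still leave several weeks of earlier walking before the items.
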